**METHOD**

**Data source, study design, and study population**

This cohort study will be based on the nationwide histopathology cohort, Epidemiology Strengthened by histoPathology Reports in Sweden (ESPRESSO)^1^, and several healthcare registers in Sweden. ESPRESSO^1^ contains data on GI-related biopsies from all 28 pathology departments in Sweden from 1965 to 2017. The Total Population Register^2^ contains details on birth, death, and migration, which was initiated in 1968. The Prescribed Drug Register^3^ collects information on medications dispensed at all pharmacies in Sweden since July 2005, including for example dispensing date, drug name, and a defined daily dose (DDD). The National Patient Register^4^ covers data on inpatient (since 1964) and outpatient (since 2001) specialist care with disease diagnoses and surgical procedures. The Cancer Register^5^ contains data from >96% of incident cancer cases since 1958. The Cause of Death Register^6^ contains information on >99% of death since 1952. The Swedish Longitudinal Integrated Database for Health Insurance and Labour Market Studies^7^ contains information on demographic and socioeconomic characteristics (e.g., education and county of residence).

The IBD patients will be identified as those with ≥ 1 biopsy indicating IBD in the ESPRESSO and ≥ 1 International Classification of Disease (ICD) code for IBD in the NPR (see **Table 1** for the definition of IBD subtypes)^8^. Such diagnostic approach yields a positive predictive value of 95%^9^.

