**Secondary analyses**

Three secondary analyses will be conducted. First, to assess the relationship between continuous statin treatment and outcomes, we will apply an as-treated analysis where we further censor the follow-up at the end of the first treatment episode, in addition to the abovementioned censoring criteria. Second, to evaluate whether cumulative duration of statin use is associated with the outcomes, we will apply a nested case-control study in statin users. Using the method of incidence density sampling, for each case exposed to statin and with later studied outcomes, we will randomly select up to five statin users who did not develop the interested outcomes (controls). They will be individually matched on age at index date, gender, IBD subtype, IBD duration, and duration of follow-up. Conditional logistic regression will be used to estimate odds ratios (ORs) with 95% CIs. The cumulative duration of statin use will be assessed between first prescription and end of follow-up, and categorized into categories (30 days-<1 year (reference group), 1-<2 years, 2-<5 years, and ≥5 years cDDD). Trends in the dose-response association will be tested by using the duration strata as an independent variable in the model. Third, we will repeat the main analysis without accounting for competing risks.

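### The duration analysis keeps at most five random controls per case although dispensing data exist for every statin user: a valid design that gives up a little precision where more than five are eligible

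*SAP*

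**What the plan says.** Under Secondary analyses, the SAP addresses cumulative duration as follows: "we will apply a nested case-control study in statin users". Controls are drawn by risk-set sampling ("Using the method of incidence density sampling"), and the cap is set in the words "we will randomly select up to five statin users", restricted to those without the outcome under study. Cases and controls are "individually matched on age at index date, gender, IBD subtype, IBD duration, and duration of follow-up"; no calipers are given. The estimator is fixed: "Conditional logistic regression will be used to estimate odds ratios (ORs) with 95% CIs". Exposure has four levels: "30 days-<1 year (reference group), 1-<2 years, 2-<5 years, and ≥5 years cDDD".

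Under Data source, study design, and study population, the SAP says that the Prescribed Drug Register "collects information on medications dispensed at all pharmacies in Sweden since July 2005", including dispensing date, drug name and defined daily dose. Identification of statin users takes the exposed cohort from this same register.

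The SAP gives no reason for the cap and plans no full-risk-set analysis of duration beside it. The as-treated analysis in the same section uses the cohort's follow-up but asks a different question.

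**The concern.** Controls are usually sampled because exposure is costly to obtain. Here it is on file for every potential control, so the cap discards eligible people without a stated gain. Conditional logistic regression accepts any number of controls per set, so neither the model nor the matching calls for a limit of five.

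Precision is what is at stake. Incident CRC and CRC-related death among statin users are likely to be few, and they are spread over four duration categories. Duration-response results are often read as support for causation, so a wider interval than the data require is unhelpful. In addition, two analysts who follow the SAP exactly but draw different controls will report different odds ratios.

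**Working it through.** **Inputs.** From the SAP: m = 5 controls at most, four duration categories, conditional logistic regression, five matching factors. Not in the SAP, so assumed: M = 20 to 40 eligible controls per case; 70 CRC cases; a share of 0.25 in the reference category and 0.30 in the top category. The SAP states no precision or power figure for this analysis, so there is none to reproduce.

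**1. Relative efficiency at the null.** Against an unlimited risk set, m controls per case retain m/(m+1) of the information:

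- m = 5: 5/6 = 0.833
- m = 20: 20/21 = 0.952
- m = 40: 40/41 = 0.976

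**2. Gain from using all eligible controls.** The ratio of standard errors, all against five, is the square root of the ratio of efficiencies:

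- M = 20: sqrt(0.833/0.952) = 0.935, so the log-OR interval is 6.5% narrower
- M = 40: sqrt(0.833/0.976) = 0.924, 7.6% narrower
- M very large: sqrt(0.833) = 0.913, about 9% narrower
- M of five or fewer: all are taken already, so the gain is 0

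**3. Away from the null.** For a binary exposure with prevalence 0.1 to 0.8 and rate ratio 0.3 to 1.5, five controls retain 0.74 to 0.93 of the unlimited-control information. The standard error is then 1.04 to 1.16 times the full one, so the null figure of 1.095 lies mid-range. A simulation with four duration categories, 100 or 200 cases and 50 or 200 people per risk set gave ratios of 1.08 to 1.10.

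**4. Dependence on the draw.** With 70 cases, the full-data variance of the top-versus-reference log-OR is about 1/(70 × 0.25) + 1/(70 × 0.30) = 1/17.5 + 1/21 = 0.105. Choosing five of M adds (1/5 − 1/M) × 0.105:

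- M = 20: 0.15 × 0.105 = 0.0157, SD 0.125
- M = 40: 0.175 × 0.105 = 0.0183, SD 0.135

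Simulation under these assumptions gave SDs of 0.124 to 0.165. At an SD of 0.14, an all-control OR of 0.70 has a two-SD band of 0.70 × exp(±0.28) = 0.53 to 0.93 over repeated draws.

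**5. The same band beside the ordinary interval.** With five controls, SE = sqrt(0.105 × 1.2) = 0.35, and the 95% CI for an OR of 0.70 is about 0.35 to 1.40. With 20 controls, SE = sqrt(0.105 × 1.05) = 0.33, and the CI is about 0.37 to 1.34. The draw band lies well inside both.

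**The case against.** The strongest reply is that nothing here is wrong. Risk-set sampling at 5:1 with conditional logistic regression is a recognised design with valid inference, and it leaves the main analysis untouched. That stands, and it is why the point is optional.

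Three stronger readings are tempting, and the SAP supports none of them.

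- **That the odds ratios are unreliable because they move with the seed.** The movement is real, but the conditional-logistic interval already includes the control-sampling variance. It is not a separate, unreported uncertainty, and the 0.53 to 0.93 band should not be quoted without the interval of about 0.35 to 1.40. Saving the seed makes a given draw reproducible.
- **That 17% of the information is always lost.** The 83% figure compares five controls with an unlimited number. Against 20 to 40 eligible controls, five retain 0.833/0.952 = 87.5% to 0.833/0.976 = 85.4%. Matching on five factors, three of them continuous in nature, may leave some cases with five or fewer controls, and the phrase up to five allows for this. Without calipers or a cohort size, nobody can say how often that happens.
- **That a Cox model is automatically the same analysis.** It is not if age, IBD duration or follow-up are matched within calipers around each case, since calipers do not form fixed strata. Nor is it if the control definition is read as removing people who become cases later.

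The rare-outcome argument also applies mainly to CRC and CRC-related death. It carries less weight for all-cause mortality, where more events are expected.

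**Conclusion.** The point holds as an efficiency remark. Where more than five controls are eligible, the cap gives up precision for no stated reason. The log-OR intervals could be about 6-8% narrower with 20 to 40 eligible controls, up to about 9% narrower with very many, and no narrower with five or fewer. These are null approximations. They rest on an assumed number of eligible controls, and the draw-variation figures also rest on an assumed 70 cases and assumed category shares.

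The point estimate depends on the draw, but the interval accounts for it. There is no bias and no invalid inference. Severity is low, and only one secondary analysis is affected.

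**What to change.** In Secondary analyses, replace "we will randomly select up to five statin users who did not develop the interested outcomes (controls)" with: *we will include all statin users still at risk and free of the outcome at the case's event date who meet the matching criteria (controls)*. Keep the matching factors and the conditional logistic regression as they are.

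Replacing the whole clause matters. If only the number five were removed, the words about not developing the outcome would remain and could still be read as excluding future cases from the risk set.

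A Cox model in statin users with time-varying cumulative duration is an alternative only if it uses the same strata and time scale.

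The cost is one clause in the SAP and a larger analysis file. No new data are needed and no bias is added.

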**Identification of primary and secondary outcomes**

Follow-up will begin at index date until the first recorded date of incident CRC, proctocolectomy, emigration, death, or end of follow-up (Dec, 2019). A patient who had a colectomy but had an intact rectum will be considered at risk of rectal cancer until proctectomy (see **Table 2** for procedure codes). The primary outcome is incident CRC (see **Table 2** for ICD codes), while secondary outcomes are CRC-related mortality and all-cause mortality (see **Table 2** for ICD codes).

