**Subgroup analyses and sensitivity analyses**

We will assess whether the associations vary by the following factors: age at the index date (<60 or ≥60 years), sex, calendar period for IBD diagnosis (1969-1999 or 2000-2018), educational attainment (0-9, 10-12, ≥13 years, or “missing”), IBD subtype (CD or UC), age at IBD diagnosis (<50 or ≥50 years), duration of IBD (<10 or ≥10 years), type of statins initially treated, and type of CRC (colon cancer or rectal cancer).

Several sensitivity analyses will be conducted. First, we will construct a model in which covariates will adjusted as time-varying variables. Second, we will exclude individuals with a history of CVD before statin initiation. Third, we will discard the first year and then first two years of follow-up from the analysis. Fourth, we will evaluate the potential influence from unmeasured confounding by calculating E-values^14^. Finally, we will perform a negative control analysis using fracture as a negative control outcome to assess potential biases in our study^15^.

Data analyses will be performed using SAS version 9.4, Stata (version 16.1), and R version 3.6.0.

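### The nested case-control analysis counts statin use up to the event with no exposure lag, so extra stopping among cases shortly before CRC or death can create a false inverse association with duration

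*SAP*

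**What the plan says.** Under Secondary analyses, the SAP plans a nested case-control study among statin users to relate cumulative duration of use to the outcomes. The exposure rule is: "The cumulative duration of statin use will be assessed between first prescription and end of follow-up". The categories are "30 days-<1 year (reference group), 1-<2 years, 2-<5 years, and ≥5 years cDDD", and the trend rule is: "Trends in the dose-response association will be tested by using the duration strata as an independent variable in the model".

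The section Identification of primary and secondary outcomes sets when a patient's time at risk stops: "Follow-up will begin at index date until the first recorded date of incident CRC, proctocolectomy, emigration, death, or end of follow-up (Dec, 2019". The primary outcome is incident CRC, and the "secondary outcomes are CRC-related mortality and all-cause mortality".

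Controls come from incidence density sampling: "we will randomly select up to five statin users who did not develop the interested outcomes (controls". On matching: "They will be individually matched on age at index date, gender, IBD subtype, IBD duration, and duration of follow-up".

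The nearest safeguard is under Subgroup analyses and sensitivity analyses: "we will discard the first year and then first two years of follow-up from the analysis". The SAP states no lag, latency window or exposure cut-off before the event.

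**The concern.** Read together, the exposure rule and the follow-up rule make a case's exposure window run to the day of CRC diagnosis or death. Patients in terminal decline, or with symptoms of a cancer not yet diagnosed, may stop preventive drugs in the preceding months. Their recorded duration is then shortened by the approaching event. A control alive and well at the same follow-up time has no such reason to stop.

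Matching on duration of follow-up gives case and controls equal time to accumulate use, but it does not correct use cut short because of the event. Correct risk-set sampling does not correct it either, so this is separate from how controls are chosen.

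The distortion points the same way as the SAP's hypothesis that statins lower risk, so a false result would read as confirmation. This is also the only duration-response analysis in the SAP.

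**Working it through.** The SAP gives no event count, expected OR or stopping data for this analysis, so there is no planned figure to reproduce. The check is by simulation with a true OR of 1.

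**Inputs from the SAP.** Four duration categories (cut points 1, 2 and 5 years), 5 controls per case, equal follow-up within a set, and conditional logistic regression with the category score as the trend term. Exposure starts in July 2006 or later and follow-up ends in December 2019, so follow-up is at most about 13.5 years.

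**How a case moves category.** Recorded duration is min(background stop, pre-event stop, event time − lag), multiplied by daily coverage where coverage is modelled. For example, take a continuous user with an event at 1.25 years who stops 6 months before. Recorded use is 1.25 − 0.5 = 0.75 years, which is the reference category. A matched control who continues has 1.25 years and falls in the next category.

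**Simulation A: 150,000 matched sets.** Assumptions not in the SAP: event times uniform from 0.25 to 13 or 8 years; background stopping 10% per year in everyone; mean coverage 0.85 (SD 0.15); a share p of cases stops a mean of m months before the event (uniform on 0 to 2m). The ORs below are for 5 years or more against under 1 year, unlagged, with the trend OR per category in brackets.

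| p, m | 13-year horizon | 8-year horizon |
|---|---|---|
| no extra stopping | 1.00 (1.00) | 1.00 (1.00) |
| 30%, 3 months | 0.94 (0.98) | 0.88 (0.96) |
| 30%, 6 months | 0.89 (0.97) | 0.79 (0.93) |
| 50%, 6 months | 0.83 (0.95) | 0.67 (0.88) |
| 80%, 6 months | 0.75 (0.91) | 0.54 (0.82) |
| 50%, 12 months | 0.69 (0.89) | 0.47 (0.79) |

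A 1-year lag returns the OR to 1.00 for m = 3 or 6. For m = 12 it leaves 0.90 (13 years) or 0.77 (8 years), and a 2-year lag returns 1.00.

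**Simulation B: cohort with risk-set sampling.** Assumptions: 2.5 events per 100 person-years, 12% per year background stopping, follow-up up to 13.5 years. The ranges cover repeat runs that differ in details such as the shape of the pre-event gap.

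| Extra stopping | No lag | 1-year lag | 2-year lag |
|---|---|---|---|
| none | 1.01–1.02 | – | – |
| 20%, mean 6 months | 0.84–0.87 | 0.97–0.99 | 0.99–1.02 |
| 30%, mean 6 months | 0.78–0.81 | 0.92–0.98 | 0.97–1.02 |
| 30%, mean 12 months | 0.66–0.69 | 0.85–0.88 | 0.95–0.96 |

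**Shape.** The unlagged ORs for 1–<2, 2–<5 and 5 or more years are 0.82, 0.82 and 0.80 (30%, 6 months) and 0.72, 0.69 and 0.67 (30%, 12 months) under the Simulation B assumptions. Most of the displacement is the reference category gaining cases, which lowers every other category against it. In Simulation A some slope appears at the extreme: 0.67, 0.61 and 0.47 (50%, 12 months, 8-year horizon).

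**The first-years discard.** If sets with under 2 years of follow-up were dropped from the case-control study, the OR for 5 years or more would move from 0.80 to 0.93 (30%, 6 months), from 0.85 to 0.95 (20%, 6 months) and from 0.67 to 0.80 (30%, 12 months). The OR for 1–<2 years would rise to 1.14 in the first of these. The one-year version changes nothing. For a case at year 7, exposure in years 6 to 7 is still counted in full.

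**The case against.** The strongest objection is that the bias is conditional. A reader might infer that the missing lag by itself manufactures a protective duration-response. It does not: with equal stopping in cases and controls the simulated OR is 1.00, and the SAP has no data on stopping before CRC or death. The same setting (30%, 6 months) gives 0.89 or 0.79 depending on the horizon. All of this stands, and it is why the effect is stated as possible and given as a range.

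Second, the category ORs would look nearly flat beyond the reference, not like a smooth dose-response. This also stands. However, the planned trend test enters the strata as one term, so the step still pulls it below 1.

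Third, the first-years discard might cover the point. The SAP does not say whether it extends to the case-control study. If it does, the two-year version reduces the bias but does not remove it, because it drops early events and leaves exposure just before later events in place.

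Fourth, a reader might infer that the study's main causal evidence is at risk, or that all three outcomes are equally affected. Neither is supported. The SAP lists this as one of three secondary analyses and gives duration-response no special standing. The main comparison is intention-to-treat from the index date in a propensity-matched cohort. One event rate was simulated, with no outcome-specific stopping pattern.

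**Conclusion.** The concern holds in conditional form. The SAP fixes an exposure window that runs to the event, and nothing else in it lags exposure. If cases stop statins more often than controls shortly before the event, the analysis can show a false inverse association and a false trend under a true null. Across the scenarios with extra stopping, the OR for 5 years or more against under 1 year ran from about 0.94 (30% stopping a mean of 3 months before, 13-year horizon) to 0.47 (50% at 12 months, 8-year horizon). These sizes rest on assumed stopping, coverage and event-time patterns, none of which is in the SAP.

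The problem is probably most relevant to the two mortality outcomes, where stopping near the end of life is plausible, and less so to incident CRC. That ranking is a judgement. The finding is confined to this secondary analysis. It is worth correcting because the change is small and the possible error favours the study hypothesis.

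**What to change.** Amend the case-control paragraph under Secondary analyses as follows:

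- Count statin use from first prescription to 1 year before the case's event date, and to the same follow-up time in its matched controls.
- Include only sets with follow-up longer than the lag.
- Repeat with a 2-year lag and report the unlagged result alongside. The repeat is needed because a 1-year lag leaves about 0.87 if 30% of cases stop a mean of 12 months before the event.
- State whether the discard of the first one and two years applies to this analysis.

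The SAP describes dispensing dates in the Prescribed Drug Register, so no new data are needed. If extra stopping is absent, lagged and unlagged results should agree apart from chance, which supports robustness.

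The cost is precision. In simulation about 16% of sets had under 1 year of follow-up and about 30% under 2 years. Sets with 1 to 2 years of follow-up also become uninformative under a 1-year lag, because all lagged durations then fall under 1 year. Informative sets fell from about 70% to 58% with a 1-year lag and 47% with a 2-year lag. These percentages assume duration is counted in calendar time. The categories are labelled in cDDD, and dispensing above one DDD per day could place some patients in higher categories sooner.

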**Subgroup analyses and sensitivity analyses**

We will assess whether the associations vary by the following factors: age at the index date (<60 or ≥60 years), sex, calendar period for IBD diagnosis (1969-1999 or 2000-2018), educational attainment (0-9, 10-12, ≥13 years, or “missing”), IBD subtype (CD or UC), age at IBD diagnosis (<50 or ≥50 years), duration of IBD (<10 or ≥10 years), type of statins initially treated, and type of CRC (colon cancer or rectal cancer).

Several sensitivity analyses will be conducted. First, we will construct a model in which covariates will adjusted as time-varying variables. Second, we will exclude individuals with a history of CVD before statin initiation. Third, we will discard the first year and then first two years of follow-up from the analysis. Fourth, we will evaluate the potential influence from unmeasured confounding by calculating E-values^14^. Finally, we will perform a negative control analysis using fracture as a negative control outcome to assess potential biases in our study^15^.

Data analyses will be performed using SAS version 9.4, Stata (version 16.1), and R version 3.6.0.

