**Identification of statin users**

Statin use will be identified from the Prescribed Drug Register by the Anatomical Therapeutic Chemical (ATC) code C10AA, including lipophilic statins (simvastatin and atorvastatin) and hydrophilic statins (pravastatin and rosuvastatin) (see **Table 2** for ATC codes). Statin users will be identified as those aged ≥ 18 years and with a statin prescription for ≥30 cumulative DDD (cDDD) from July, 2006 or later. The date that an individual first attained a cDDD ≥ 30 for a statin will be defined as the index date for statin exposure. Individuals who had any statin prescription before July 2006, before IBD diagnosis or before the first attainment of cDDD ≥ 30 will be excluded from the analysis to ensure a new-user design. We will use the intention-to-treat analysis as the main analysis.

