**Two-step matching process**

A two-step matching process will be applied to establish the cohort. In the direct matching step, statin users and non-statin users will be matched on age at IBD diagnosis (<18, 18-<40, 40-<60, and ≥60), sex, IBD subtype (CD or UC), and calendar year at IBD diagnosis (1969-1989, 1990-1999, 2000-2009, 2010-2018). IBD-unclassified will not be considered in this project due to diagnostic uncertainty. To ensure similar opportunities for care and treatment^10^, non-statin users should have a random drug prescription (except IBD medications, see **Table 2** for ATC codes) within three months before or after the start date of statin treatment in the matched statin users. All identified non-statin users will be assigned the same index date as the index statin user. We will exclude individuals who had a record of migration, received a colectomy, or had a diagnosis of any of the following diseases before the index date: cancers, human immunodeficiency virus/ acquired immunodeficiency syndrome, primary immunodeficiency disease, end-stage renal disease, severe liver failure, and any organ transplantation (see **Table 2** for procedure and ICD codes).

In the propensity score matching step, statin users and non-statin users will be matched in a 1:1 ratio by using a greedy nearest-neighbor matching algorithm without replacement, with a caliper of 0.2 standard deviation of the logit of the propensity score^11^. A logistic regression model will be used to calculate the propensity score after adjusting for the below demographic and socioeconomic characteristics, comorbidities, and co-medications identified up to and including the index date.

- Age at IBD diagnosis, years (continuous);
- Duration of IBD, years (continuous);
- Number of healthcare visits (continuous);
- Country of birth (Nordic countries or others);
- Education (0-9, 10-12, ≥13 years, or missing);
- Comorbidities (yes/no, see Table 2 for detail): gastrointestinal diseases, intestinal infections, cardiovascular diseases, obesity/dyslipidemia, type 1 and type 2 diabetes, autoimmune diseases, obstructive sleep apnea, chronic obstructive pulmonary disease, and myositis;
- Medications (yes/no, see Table 2 for detail): antibiotics, proton pump inhibitor, antiviral medications, IBD medications, non-aspirin anti-platelet medications, aspirin, non-statin lipid lowering medications, anti-diabetic medications, anticoagulation medications, and anti-arrhythmias medications.

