**STATISTICAL ANALYSES**

Incidence rates and their differences with 95% confidence intervals (CIs) for incident CRC, CRC-related mortality, and all-cause mortality will be calculated using Poisson regression. To account for competing risk, we will apply subdistribution hazard model to estimate hazard ratios (HRs) and 95% CIs, using time since index date as the underlying time scale. Cumulative incidence function will be applied to estimate the cumulative incidence of the primary and secondary outcomes.

We will calculate the number needed to treat (NNT)^12^ to avoid one event at 10-year since it is the most commonly used time period for CRC^13^.

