| Rosuvastatin | C10AA07 |
| **Outcomes** | **ICD code** ^a^ |
| Incident colorectal cancer (CRC) ^b^ | ICD-7: 153-154, but not 1541 (anal cancer) or 1534 (appendiceal cancer) |
| CRC-related mortality | ICD-10: C18-20, but not C181 (appendiceal cancer) |
| All-cause mortality | ICD-10: A00-U99 |
| **Proctocolectomy and colectomy** | **Procedure code** |
| Proctocolectomy ^c^ |  |
|  | Sixth version (1969-1996): 4652, 4653, 4654 |
|  | Seventh version (1997-): JFH20-JFH40 |
| Colectomy with an intact rectum ^d^ |  |
|  | Sixth version (1969-1996): 4650, 4651 |
|  | Seventh version (1997-): JFH00, JFH01, JFH10, JFH11, JFH96 |
| Rectum amputation after a colectomy with an intact rectum ^e^ |  |
|  | Sixth version (1969-1996): 4820, 4821, 4822, 4828 |
|  | Seventh version (1997-): JGB00-JGB97 |
| **Exclusion criteria** | **ICD-10 code/procedure code** |
| Cancer | C00-C97, except non-melanoma skin cancer (C44) |
| HIV/AIDS | B20-B24, F024, O987, R75, Z114, Z219, Z711 |
| Primary immunodeficiency disease | D71, D80–D84 |
| Severe liver failure | B150, B160, B162, B190, K704, K72, K766, I85 |
| End-stage renal disease | N18.5,  N18.6, Z49, Z99.2, Z94.0; Procedure codes: 9200; V9200; 9212; V9212; 9314; V9531; DR012; DR013; DR016; DR024; QF006; 9211; V9211; 9213; V9213; V9532; DR015; DR023; DR055; DV056; 9219; V9219; 9223; V9223; DR017; DR020; DR055; DR056; 6070; KAS10; KAS20 |
| Any organ transplantation | Swedish surgery codes (KVÅ codes): KAS, FQA, FQB, GDG, JJC |
| **Comorbidities** | **ICD-10 code** |
| Gastrointestinal diseases | K00-K99 |
| Intestinal infections | A00-A09 |
| Cardiovascular diseases | I00-I99 |
| Obesity/dyslipidemia | E78 , E65, E66 |
| Type 1 and type 2 diabetes | E10-E14 , O24 |
| Autoimmune diseases | E035, E039, E050, E055, E059, E063, E065, G35, M05-M09, M32, L40 |
| Obstructive sleep apnea | G473 |
| Chronic obstructive pulmonary disease (only if diagnosed ≥40 years) | J41-J44 |
| Myositis (no adequate codes present for rhabdomyolysis) | M60 |
| **Medications** | **ATC code** |
| Antibiotics | J01 |
| Proton pump inhibitor | A02BC |
| Antiviral drugs | J05 |
| IBD medications |  |
| Immunomodulators |  |
| Azathioprine | L04AX01 |
| Mercaptopurine | L01BB02 |
| Methotrexate | L04AX03/L01BA01 |
| Anti-TNF treatment |  |
| Infliximab | L04AB02 (L04AA12 before 2008) |
| Adalimumab | L04AB04 (L04AA17 before 2008) |
| Golimumab | L04AB06 |
| Vedolizumab | L04AA33 |
| Systemic corticosteroids |  |
| Betamethasone | H02AB01 |

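### The first sensitivity analysis adjusts an exposure fixed at the index date for covariates updated after it, so it cannot test the robustness of the intention-to-treat estimate

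*SAP*

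**What the plan says.** Under Identification of statin users, the SAP fixes the exposure contrast: "We will use the intention-to-treat analysis as the main analysis". Exposure is therefore classified once, at the index date.

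Under Two-step matching process, the covariates enter the propensity score with "comorbidities, and co-medications identified up to and including the index date". The comorbidities include "gastrointestinal diseases, intestinal infections, cardiovascular diseases, obesity/dyslipidemia, type 1 and type 2 diabetes". The medications include "aspirin, non-statin lipid lowering medications, anti-diabetic medications, anticoagulation medications, and anti-arrhythmias medications". The number of healthcare visits is also listed. Table 2 annotates one covariate as "Myositis (no adequate codes present for rhabdomyolysis", a reference to muscle injury.

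Under Statistical analyses, the main model is given as: "To account for competing risk, we will apply subdistribution hazard model to estimate hazard ratios (HRs) and 95% CIs".

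Under Subgroup analyses and sensitivity analyses, the first item is: "we will construct a model in which covariates will adjusted as time-varying variables". It does not say which covariates are updated, how or with what lag, or which regression model is used. No method for covariates affected by earlier treatment is named.

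**The concern.** Confounding of a contrast set at the index date comes from what precedes that date. Values recorded later cannot confound it. They can be consequences of it: a statin may change later cardiovascular disease, diabetes, myositis, use of other lipid-lowering drugs and visit frequency. Putting their updated values beside the fixed exposure does two things. It takes out the part of the effect that runs through them. It also conditions on a common effect of statin use and any unmeasured cause shared with the outcome, which creates an association that was not there.

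A gap from the main result would naturally be read as residual confounding when it may be over-adjustment. Agreement would be read as reassurance when the model estimates something else.

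A second, conditional difficulty concerns CRC and CRC-related mortality. In a subdistribution model, people who die of a competing cause stay in the risk set, and diagnoses, dispensings and visits do not exist for them after death.

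**Working it through.** The SAP gives no figure on this point, so there is none to reproduce. The check is a reading of the sections plus illustrative simulation. All rates and effects below are assumptions.

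**Step 1: what is estimated.** Let A be exposure at the index date and M(t) an updated covariate. The total effect is exp(β) from log λ(t) = α(t) + βA. The planned analysis reports exp(β) from log λ(t) = α(t) + βA + γM(t). If A affects M, the second β excludes the path through M, and it is also biased as a direct effect if M and the outcome share an unmeasured cause U.

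**Step 2: CRC, strong inputs.** 3 million people, 1:1, 13 years, piecewise-exponential Poisson fit. CRC 0.002/yr, death 0.02/yr, M onset 0.04/yr, direct HR 0.70. Standard error of log HR 0.006 to 0.008. In the subdistribution columns M is frozen at death.

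| Scenario | Cause-specific: without M, with M(t) | Shift | Subdistribution: without M, with M(t) | Shift |
|---|---|---|---|---|
| Statin lowers M (×0.6); M doubles CRC, triples death | 0.661, 0.701 | +0.040 | 0.670, 0.707 | +0.037 |
| Statin raises M (×1.4); M raises CRC ×1.5, death ×2 | 0.714, 0.694 | −0.020 | 0.711, 0.690 | −0.021 |
| Statin lowers M (×0.6); M has no effect on CRC, triples death; U raises M and CRC 4-fold | 0.711, 0.748 | +0.037 | 0.726, 0.759 | +0.033 |
| Statin does not affect M | 0.703, 0.703 | 0 | 0.703, 0.703 | 0 |

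The third row is the collider case: adjustment moves the estimate away from the direct effect of 0.70. The fourth row shows that nothing happens unless the statin affects the covariate.

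**Step 3: CRC, milder inputs.** 10 years, cardiovascular disease (CVD) onset 0.03/yr, CRC 0.002/yr, statin lowers CVD by 25%, direct HR 0.80. CVD without effect on CRC: 0.786 to 0.786. CVD raising CRC 1.2-fold: 0.782 to 0.786. A 2-fold unmeasured common cause: 0.792 to 0.796. Shifts are 0 to 0.004.

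**Step 4: all-cause mortality.** Statin lowers CVD by 25%; CVD triples mortality.

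| Scenario | Without CVD, with CVD(t) | Shift |
|---|---|---|
| Direct HR 0.95 | 0.904, 0.946 | 0.042 |
| Direct HR 0.95; U with 30% prevalence, 4-fold on CVD and death | 0.919, 0.984 | 0.065 |
| Same U, no direct effect | 0.951, 1.027 | 0.076 |
| U 2-fold, no direct effect | 0.951, 1.007 | 0.056 |
| U 1.5-fold, no direct effect | 0.954, 1.004 | 0.050 |
| U 4-fold, no direct effect, 30% with CVD at baseline | 0.968, 1.000 | 0.032 |

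With death at 0.02/yr and CVD onset varied from 0.02 to 0.06/yr over 13 years, the first three rows become 0.88–0.91 to 0.95, 0.90–0.92 to 0.98–1.00, and 0.94–0.96 to 1.02–1.04. The gap widens with onset; in the last case it runs from 1.02 − 0.96 = 0.06 to 1.04 − 0.94 = 0.10.

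**Step 5: the subdistribution risk set.** The section on outcomes states: "Follow-up will begin at index date until the first recorded date of incident CRC, proctocolectomy, emigration, death, or end of follow-up". Observation ends at death, so any later M(t) must be invented. Freezing M at death, against letting it continue unobserved, gave 0.707 against 0.702, 0.690 against 0.694, and 0.759 against 0.751 in the first three scenarios of step 2. The differences are 0.004 to 0.008: small here, but resting on values that are not in the data. All-cause mortality has no competing death, so this step does not concern it.

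**The case against.** The strongest reply is that the SAP says only that a model will be constructed. A reader might infer that time-varying covariates are to go into the subdistribution model and that the analysis is therefore invalid as planned. The text does not support that as fact. The SAP uses other models elsewhere (Poisson, conditional logistic, and a repeat of the main analysis that ignores competing risks), and a cause-specific model may be meant. This stands: the subdistribution point is conditional.

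A reader might also infer that the analysis could turn a benefit into apparent harm. A clear reversal appeared only with a 4-fold unmeasured common cause, no direct effect and nobody with CVD at baseline. With a 2-fold or 1.5-fold cause the adjusted value is essentially the assumed direct effect of 1. Baseline CVD is plainly expected, since it is a matching covariate and a later sensitivity analysis excludes patients who have it. If covariates are coded as history, those patients cannot change value. Likewise the gastrointestinal category, K00-K99, contains the IBD codes K50 and K51 and can scarcely vary. This stands too.

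Updating covariates that statins do not affect is harmless, and an estimate adjusted for post-index covariates can be a legitimate supplementary question if labelled as such. A baseline-adjusted Cox model would largely repeat the third secondary analysis. Both points shape the fix. None of this rescues the analysis as a robustness check: time-varying confounding needs a time-varying exposure, and this item specifies none.

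**Conclusion.** The point holds as a fault in one sensitivity analysis. With exposure fixed at the index date, adjustment for post-index covariates cannot correct confounding of that contrast and may introduce over-adjustment and collider bias. Its agreement or disagreement with the main result is not evidence about robustness.

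Under the assumed inputs the shift in the HR is nil to about 0.04 for CRC, the primary outcome. For all-cause mortality, if statins lower CVD by 25% and CVD triples mortality, it is about 0.04 to 0.08 at central inputs, 0.03 with 30% baseline CVD, and up to 0.10 at the highest onset rate tried. It is zero where statins do not affect the covariate. The SAP supplies none of these inputs, so the figures show direction and order of size only.

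The missing covariate values after death are a further problem only for CRC and CRC-related mortality, and only if the subdistribution model is retained. A reader might infer that the main result is compromised; it is not, because its covariates are measured no later than the index date.

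**What to change.** In the intention-to-treat analysis, adjust only for covariates measured up to the index date. Use time-updated covariates only in inverse-probability-of-censoring weights for the as-treated secondary analysis, where stopping treatment may depend on them, or in the weights of a marginal structural model for time-varying statin use.

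If the time-varying model is kept, fit it as a cause-specific Cox model, list the covariates with their update rule and lag, and label it as supplementary and adjusted for post-index covariates, not as a robustness check of the total effect.

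The cost is a change of SAP wording, a small amount of extra analysis work, and wider intervals from the weighting. No new data are needed beyond the registers already used.
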